## 3. Procedure

### 3.1. Recruitment

The PRE-IOP study will recruit 120 pregnant female volunteers. The obstetrician will propose the study to all women between 15 and 18 weeks of amenorrhea and between 18 and 40 years of age. If the pregnant woman accepts to be included in the study, then the obstetrician will give her a trial information sheet and a consent form, and an inclusion visit will be planned with a dentist. The total number of pregnant women screened and recruited will be referenced. Participants will not receive any financial compensation.

### 3.2. Allocation of Interventions

#### 3.2.1. Allocation

In the PRE-IOP trial, participants will be randomly assigned at the start of the trial to one of four arms: Arm 1—Interactive sonic toothbrush, DiamondClean 9000 Sonicare (Philips^®^, Suresnes, France); Arm 2—Non-interactive sonic toothbrush, HydroSonic Easy (Curaden^®^, Kriens, Switzerland); Arm 3—Manual toothbrush, Oral-B 123 (Procter & Gamble^®^, Asnières-sur-Seine, France); and Arm 4—Manual toothbrush Curaprox CS 5460 (Curaden^®^, Kriens, Switzerland)) (Table 1). Random arm allocation will be computer-generated by the study manager using e-CRF Voozalyon 1.3 (Voozanoo, Caluire, France). Participants will remain in the same arm during the study period. Eligible pregnant women will be included in the study and numbered according to the inclusion order up to the number of subjects (*n* = 120, 30 pregnant women per group).

#### 3.2.2. Blinding

There will be a clear distinction between the assignment generator and the individuals responsible for carrying out the assignments. Intervention implementation will be conducted by staff who are not implicated in the process of data collection. To ensure impartiality, during the assessment and analysis phase, statisticians, clinical research associates and clinicians will not know the group to which the participant belongs. The identification codes will be securely held by the study monitor and will remain sealed until the conclusion of the study to maintain confidentiality and prevent bias.

### 3.3. Data Collection, Management and Analysis

#### 3.3.1. Data Collection Methods

An eCRF, specific to the PRE-IOP study, will be created by a data manager from ArcaLyon (Lyon, France). The software used will be the ECRF ‘EVOOZ’, version 4.90, hosted on an HDS server located in France. This software conforms to the recommendations of the FDA on computerized systems for the management of clinical trials (Guidance for Computerized Systems Used in Clinical Trials) and FDA recommendations on electronic signature (21CFR part 11). Only data required for the protocol and scientific publication will be recorded in the eCRF. Other patient information required for follow-up outside this study will be recorded in the medical dossier. This e-CRF will assign to each pregnant woman a unique identification code that will permit the labeling of all documents, forms and data files. Thus, data recorded by investigators for each participant will be anonymized according to the Data Protection Act. As data are collected, it must be completed by authorized persons (investigators) with their own identifiers, according to the Data Protection Act. During the entry, the data are immediately checked thanks to consistency checks. The person in charge of filing must validate and justify any value change in the eCRF. Entries and modifications are subject to an audit trail.

The quality, precision and relevance of all input data will be the responsibility of the investigator. As such, each page of the patient’s eCRF should be dated and signed electronically by the investigator to signify their agreement and their responsibility regarding the data collected.

#### 3.3.2. Data Management

Experimental and personal data will be analyzed using a unique identification code, ensuring the exclusion of any personal characteristics. The subjects could be identified using a subject re-identification file, which will be securely maintained solely at the clinical study site. The signed informed consent documents will also be kept exclusively at the clinical study site for confidentiality and privacy purposes.

#### 3.3.3. Data Analysis Methods

Statistical analysis will include the production of descriptive data summaries, modeling of data with a mixed (linear) model and assessment of correlations between bleeding rates. SPSS 12.0 (SPSS Inc., Chicago, IL, USA) will be used to calculate descriptive statistics (means, standard deviations and percentages). For repeated measurements at different times during the study, the SUDAAN 7.0 test (Research Triangle Institute, Research Triangle Park, NC, USA) will be used to perform statistical tests (*p*-values). The mixed linear model to explain the evolution of the quantification of bleeding over time as a function of certain independent variables first requires working on the log transform of the quantifications of bleeding. Then, in the linear mixed model, the estimated coefficients are tested for each independent variable, with the null hypothesis being that the estimated coefficient is equal to zero, at the threshold of 0.05. The fixed effects are all the independent variables that we want to test (age, CSP, experimental group, etc.), with the random effect being the subject factor, on which the four clinical bleeding probing analyses are repeated.

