### 2.6. Outcomes

#### 2.6.1. Primary Outcome Measures

Primary outcome will be the change in the incidence of gingival bleeding in pregnant woman (time frame: 3 months).

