#### 2.6.2. Secondary Outcome Measures

Secondary outcome measures will compare the effectiveness of the toothbrushes tested on the clinical changes in (i) gingival inflammation, (ii) dental plaque, (iii) gingival attachment and (iv) periodontal pocket (time frame: all outcomes will be measured at baseline (T1), 1 month/T1 (T2) and 3 months/T1 (T3))

Secondary outcomes measures will also be to evaluate (i) oral hygiene attitudes and practices (time frame: baseline (T1)), (ii) attitudes and practices in relation to the toothbrush tested (time frame: 1 month/T1 (T2) and 3 months/T1 (T3)) and (iii) assessment of the acceptability of the toothbrush tested (time frame: 1 month/T1 (T2) and 3 months/T1 (T3)).

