### 2.9. Sample Size

The reduction in gingival bleeding was considered the primary outcome variable and an estimate of a mean difference in reduction was used to calculate the sample size, when the two-sided differences in means between groups (treatment effect) were 5% (estimation extracted from ongoing project in pregnant women in Senegal; unpublished data), with a standard deviation of 10%. Using this estimate with an alpha risk of 5% and statistical power of 90% resulted in the required number of subjects per group of 25. Assuming a potential dropout rate of 20%, 30 participants per group were determined as a target for patient inclusion.

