## 4. Expected Results

The aim of the PRE-IOP randomized controlled trial is to compare the biofilm control effectiveness in pregnant women with four different toothbrushes: two manual toothbrushes and two sonic toothbrushes. The primary endpoint is the evolution in gingival bleeding over the different study periods. In addition to these clinical data, questionnaires on the acceptability of the toothbrushes tested will be analyzed to determine which of the toothbrushes tested is most acceptable to pregnant women. Clinical relevance will allow us to ensure that the outcome of the trial corresponds to a sufficiently large effect on a clinically relevant endpoint. We expect to observe significant differences in the efficiency of the four toothbrushes in disorganizing oral biofilm. One or more of the toothbrushes could prove more effective than the others, which would suggest that the choice of toothbrush has an impact on the reduction in oral biofilm.

These results would support the hypothesis that selecting the appropriate toothbrush, with the adequate brushing technique, can contribute to improving patients’ oral health. Also, these outcomes will provide decision-making support for healthcare professionals involved or not in oral health, to recommend the best devices.

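### The only treatment test named for the mixed model, a group coefficient on repeated bleeding levels, does not match the primary outcome of change over 3 months

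*Protocol article*

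**What the plan says.** Section 2.6.1 of the protocol article defines the primary outcome as the "change in the incidence of gingival bleeding in pregnant woman (time frame: 3 months"). Section 2.9 sizes the trial on the same kind of quantity: "an estimate of a mean difference in reduction was used to calculate the sample size". Section 4 restates it more loosely, without a single time point: "The primary endpoint is the evolution in gingival bleeding over the different study periods".

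Section 3.3.3 gives the analysis. Bleeding is log-transformed and put in a linear mixed model intended to describe its evolution over time. On the terms it says: "The fixed effects are all the independent variables that we want to test (age, CSP, experimental group, etc". The coefficient of each independent variable is tested against zero at 0.05. The random effect is the subject, "on which the four clinical bleeding probing analyses are repeated". The same section assigns p-values elsewhere too: "For repeated measurements at different times during the study, the SUDAAN 7.0 test" is to supply them.

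On the schedule, Section 2.6.2 says "all outcomes will be measured at baseline (T1), 1 month/T1 (T2) and 3 months/T1 (T3"). Section 2.7.3 has two follow-up visits after T1, and Table 2 marks bleeding on probing at T1, T2 and T3 only.

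**The concern.** The question is whether arms differ in how much bleeding falls over 3 months. The test named is whether arms differ in the level of repeated bleeding measurements. These are different quantities. T1 is the inclusion examination, before any effect of the study brush, so randomisation makes the expected group difference there zero. If T1 is one of the repeated responses and group enters only as a main effect, that zero is averaged into the treatment estimate, together with any chance imbalance at baseline.

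At stake is whether the primary result answers Section 2.6.1 at all. Because no contrast is named, several candidates also stay open: the overall group effect, a group-by-visit term, or the difference at T3. The choice could then be made after the data are seen.

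**Working it through.** **The plan's own figure.** Section 2.9 gives a difference of 5, SD 10, two-sided alpha 5% and power 90%, and states 25 per group. The standard formula gives n = 2 × (1.960 + 1.282)² × 10² / 5² = 84.06, so 85 per group. The stated 25 does not reproduce. That is a separate matter, used here only for context: at 25 per group the standard error is 10 × √(2/25) = 2.83, and power is Φ(5/2.83 − 1.96) = 0.42. The article gives no figure for the mixed model itself.

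**What the group coefficient estimates.** In a balanced random-intercept model without group-by-visit, the group coefficient is the plain average of the visit-specific group differences. With the T3 difference set to 1 (or 5 points):

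| Examinations in the response | Effect at each | Share kept | Shortfall | 5 points becomes |
|---|---|---|---|---|
| T1, T2, T3 | 0, 1, 1 | 2/3 | 33% | 3.33 |
| T1, T2, T3 | 0, 1/2, 1 | 1/2 | 50% | 2.50 |
| T1, T2, T3 (linear growth) | 0, 1/3, 1 | 4/9 | 56% | 2.22 |
| T1, T2, T3 | 0, 0, 1 | 1/3 | 67% | 1.67 |
| Four, baseline included | 0, 1, 1, 1 | 3/4 | 25% | 3.75 |
| T2, T3 only | 1, 1 | 1 | 0% | 5.00 |
| T2, T3 only (linear growth) | 1/3, 1 | 2/3 | 33% | 3.33 |

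Mixed models fitted to simulated data (2,000 women in each of two arms, three visits, true T3 effect 5) agree. With full effect by T2 the group coefficient was 3.31, with or without a visit term. With linear growth it was 2.39. The group-by-T3 term gave 5.18 and 4.90. So a missing visit term does not cause the shortfall; the missing interaction or baseline handling does.

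**If an interaction is fitted.** With T1 as reference, the coefficient of group becomes the baseline difference. The differences in change move to the group-by-visit coefficients, which Section 3.3.3 does not name.

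**Power for one pair of arms.** Assumptions: 25 per arm, SD of change 10, equal correlation ρ between visits (not in the article, so a range is shown), raw scale. Then the variance at one visit is s² = 100 / [2(1 − ρ)]. The variances per woman are s²(1 + 2ρ)/3 for the mean of three visits, 100 for the T3 change, and s²(1 − ρ²) for baseline-adjusted T3. In each case SE = √(2 × variance / 25) and power = Φ(effect/SE − 1.96).

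Example at ρ = 0.5, where s² = 100:
- Mean of three visits, full effect by T2: SE = √(2 × 66.67/25) = 2.31, power Φ(3.33/2.31 − 1.96) = 0.30.
- Baseline-adjusted T3: SE = √(2 × 75/25) = 2.45, power Φ(5/2.45 − 1.96) = 0.53.

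| Test | ρ = 0.3 | ρ = 0.5 | ρ = 0.7 |
|---|---|---|---|
| Group main effect, full effect by T2 | 0.48 | 0.30 | 0.17 |
| Group main effect, linear growth | 0.25 | 0.16 | 0.10 |
| Change at T3 | 0.42 | 0.42 | 0.42 |
| Baseline-adjusted T3 | 0.59 | 0.53 | 0.48 |

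**The count.** Section 3.3.3 has four repeated bleeding analyses. Sections 2.6.2 and 2.7.3 and Table 2 have three. T0 in Table 2 carries no oral examination, and leaving out T1 would give two.

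**The case against.** The strongest reply is that the article does not fix the model this tightly. The list of fixed effects is open, the model is meant to describe evolution over time, and a condensed article may leave visit, interaction and baseline terms to a fuller document. That stands: the terms are unnamed, not excluded. A reader might infer that the plan rules them out, and the text does not support that. It also never says outright that T1 is a response; this is the natural reading of modelling all the repeated examinations, but it is an inference. With T2 and T3 alone in the response and full effect by T2, there is no shortfall.

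If an interaction were fitted, its coefficients could be tested under the same rule, and they are differences in change. That is also right, but none is designated as the answer to the primary question.

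A reader might take one third as the dilution. It needs three visits and full effect at 1 month; Section 3.3.3's own count of four gives one quarter. A reader might also infer that power must fall. It need not: at ρ = 0.3 with full effect by T2, the main effect has 0.48 against 0.42 for the change score, because its standard error is smaller too.

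The figures are on the raw scale, while the model is on the log scale. The same averaging applies to log differences, but a log coefficient is not the percentage-point difference of Section 2.9, so the point and power values are illustrative.

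Finally, SUDAAN is cited with version and vendor just as SPSS is. It may simply be the software that produces the p-values, so two competing tests are not established.

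What survives is that Section 3.3.3 does state a response, a random effect, a treatment term, a null hypothesis and a threshold, and these do not match Sections 2.6.1 and 2.9.

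**Conclusion.** The point holds as a mismatch between the named test and the primary outcome, and as a contradiction in the number of examinations. If T1 is in the response and no interaction is fitted, the group coefficient understates the 3-month difference by 25% to 67% over the onset patterns examined. The exact figure depends on the number of examinations and how quickly the effect appears, neither of which the article settles.

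Loss of power against a change score is conditional on the within-woman correlation. The baseline-adjusted T3 contrast has the highest power at each correlation examined (0.59, 0.53 and 0.48), under the assumptions listed with the table. The discrepancy between four and three examinations depends on none of these assumptions.

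**What to change.** State one primary analysis in Section 3.3.3 and in any analysis plan:

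- Response: bleeding at T2 and T3. Fixed effects: T1 bleeding (on the same scale as the response), visit, group and group-by-visit. Allow for within-woman correlation.
- Primary contrast: the baseline-adjusted group difference at T3. With T1 as covariate, this equals the adjusted group difference in change from T1 to T3, so it answers Section 2.6.1 directly. Align the wording in Section 4 with it.
- Reconcile the four repeated bleeding analyses with the three scheduled examinations.
- Say whether SUDAAN is the software for this model or a supportive analysis.

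Keeping T1 as a response and naming the group-by-T3 term would also target the difference in change, but at the correlations examined the baseline-adjusted contrast is more precise than the plain change score.

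The cost is wording only: every measurement is already scheduled. It should be settled before unblinding, so that the contrast is not chosen from the results.

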#### 2.7.3. Follow-Up Visits (T2 and T3)

Two visits will be made after the inclusion of pregnant woman at T1. Visit T2 will occur one month after T1 and visit T3 will occur three months after T1 (Table 2). At each visit, an oral clinical examination and a questionnaire regarding oral hygiene attitudes and practices in relation to the toothbrush used, specific for each arm of the study (Supplementary Files S2–S5), will be performed. 

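### The bleeding model names only a random subject effect; if correlation falls over visits at 0, 1 and 3 months, a test of the 3-month change would run at about 5.6–10% rather than 5%

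*Protocol article*

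**What the plan says.** All references are to the protocol article.

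- **Primary outcome (2.6.1):** "Primary outcome will be the change in the incidence of gingival bleeding in pregnant woman", with a 3-month time frame. Section 4 describes the primary endpoint as how bleeding evolves over the study periods.
- **Visits (2.7.3):** "Visit T2 will occur one month after T1 and visit T3 will occur three months after T1". Table 2 agrees: bleeding on probing is recorded at T1, T2 and T3, that is, at 0, 1 and 3 months.
- **Model (3.3.3):** its purpose is given as "The mixed linear model to explain the evolution of the quantification of bleeding over time", after "working on the log transform of the quantifications of bleeding". On fixed effects: "The fixed effects are all the independent variables that we want to test (age, CSP, experimental group, etc"; neither visit nor a group-by-visit term is named. On dependence within a woman: "with the random effect being the subject factor, on which the four clinical bleeding probing analyses are repeated". Coefficients are tested with "the null hypothesis being that the estimated coefficient is equal to zero, at the threshold of 0.05".
- **Repeated-measurement p-values (3.3.3):** "For repeated measurements at different times during the study, the SUDAAN 7.0 test" is named for these. Its variance estimator is not stated.

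**The concern.** The dependence model is stated in the singular: one random effect, the subject. Read plainly, that is a random intercept. With independent residuals it implies the same variance at every visit and the same correlation between every pair of visits (compound symmetry). Every within-woman change then has the same model variance, whether the visits are one month or three months apart.

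The visits are unequally spaced, and the 3-month time frame of the primary outcome is the longest interval. Measurements three months apart may well correlate less than measurements one month apart. If so, the pooled residual variance is too small for the T1–T3 change and too large for the T1–T2 change. Confidence intervals for the between-brush difference in 3-month change would be too narrow and its p-values too small.

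**Working it through.** **Inputs from the article.** Three visits at 0, 1 and 3 months (2.7.3, Table 2); four equal arms, planned at 25 evaluable women each (2.1, 2.9); threshold 0.05 (3.3.3). Within-woman correlations and visit-specific SDs are not given, so those below are assumptions. Data are taken as complete, with no true difference between brushes.

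**Formula.** Let V be the true 3×3 covariance of the three measurements, P = I − J/3 with J the 3×3 matrix of ones, and σ² the residual variance of the random-intercept model with group-by-visit means. The model estimates σ² as trace(PV)/2. Its variance for any change is 2σ², which is the average of the three true pairwise change variances. With

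k = true variance of the T1–T3 change / 2σ²,

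the real two-sided size is 2·[1 − Φ(1.96/√k)].

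**The plan's own figure.** With equal variances and all correlations 0.5, each change variance is 2(1 − 0.5) = 1, so k = 1 and the size is 5.0%. The stated threshold is reproduced when compound symmetry is true.

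**Two cases by hand** (correlations in the order T1–T2, T1–T3, T2–T3)

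- 0.7, 0.5, 0.6 with SD 10 at every visit: change variances 60, 100, 80; average 80. 1/k = 80/100 = 0.80. Size = 2·P(Z > 1.96·√0.80) = 2·P(Z > 1.753) ≈ 8.0%. The standard error is understated by 1 − √0.80 ≈ 11%. For the 1-month change, k = 60/80 = 0.75 and the size is about 2.4%.
- 0.60, 0.50, 0.55 with SD 1: change variances 0.8, 1.0, 0.9; average 0.9. k = 1.0/0.9 = 1.11 and the size is 6.3%.

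**Range of assumptions**

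| Assumed truth | k | Size, 3-month change | Size, 1-month change |
|---|---|---|---|
| Compound symmetry | 1.00 | 5.0% | 5.0% |
| Stable woman effect + AR(1) + measurement noise | 1.05–1.10 | 5.6–6.2% | 3.7–4.4% |
| Mild decay (0.60, 0.50, 0.55) | 1.11 | 6.3% | 3.8% |
| AR(1) in time, 1-month correlation 0.3 | 1.13 | 6.5% | 3.0% |
| AR(1) in time, 0.5 | 1.24 | 7.8% | 2.0% |
| AR(1) in time, 0.7 | 1.34 | 9.1% | 1.2% |
| AR(1) in time, 0.9 | 1.45 | 10.4% | 0.7% |
| Equal correlation 0.5, visit SDs 1, 1.3, 1.1 | 0.84 | 3.2% | 5.6% |
| Equal correlation 0.5, visit SDs 1, 0.8, 0.8 | 1.09 | 6.0% | 6.0% |

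**Simulation check** (four arms of 25, 20,000 runs per scenario)

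- Pairwise 3-month contrast under AR(1) with 1-month correlation 0.3, 0.5, 0.7, 0.8, 0.9: 6.6%, 7.9%, 9.1%, 9.5%, 10.5%.
- Joint 3-df comparison of the four arms under the same truths: 7.6% to 14.3%.
- Group effect averaged over visits: 4.7% to 5.2% in all scenarios run.
- 3-month change tested with its own variance, which with complete data is what an unstructured covariance does for this contrast: 4.7% to 5.3% in all scenarios run.

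**The case against.** **The error rate is not a fact of the documents.** A reader might infer that the primary test will run at 7–10%. The article does not support that. It gives no within-woman correlation and no visit-specific variance. The SD of 10% in 2.9 is on the percentage scale, whereas the model is on the log scale. Values of 7–10% need fairly strong decay. A stable woman effect with measurement noise gives about 6%, compound symmetry gives exactly 5%, and unequal visit variances can take the size below 5%. This objection stands, and it is why the size is stated conditionally.

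**The residual structure is not spelled out.** The article does not say that the residuals are independent, and covariance detail is often left to an analysis plan. This stands in part: that the subject effect is the sole dependence is a reading of what is named. But the article does describe the dependence model, and a different structure would alter that description as well as add detail to it.

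**The one treatment coefficient named is not inflated.** Experimental group is listed; visit and group-by-visit are not. With complete data, a group effect averaged over visits keeps its size. That is correct. However, such an average includes baseline and does not measure change. Sections 2.6.1, 3.3.3 and 4 all put the question as change or evolution over time, and a between-brush test of that question is a group-by-time contrast.

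**SUDAAN may use a robust variance.** It may, but its estimator is not stated, so no error rate can be attached to its p-values in either direction. The mixed-model coefficients are separately tested at 0.05, so naming SUDAAN does not settle which p-value answers the primary question.

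**The repeated unit is unclear.** The text speaks of four repeated bleeding analyses, while the schedule has three examinations; 2.7.2 also records four sites per tooth. The calculation follows the three scheduled visits. The ambiguity is real and should be removed.

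**Conclusion.** The concern holds in conditional form. The only within-woman dependence the article names is a random subject effect. With otherwise independent residuals, that forces equal model variances on the 1-month and 3-month changes. If correlation declines over 0, 1 and 3 months, a group-by-visit test of the 3-month change has a real size of about 5.6–10% against a nominal 5%, and the 1-month test is conservative. With equal correlations and equal variances nothing is lost. With equal correlations and unequal visit variances the size lies at about 3–6%, so even the direction is not guaranteed.

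These figures rest on assumed correlations, complete data and a 3-month contrast that the article implies but does not write out. The change is worth making because the remedy is cheap, held the size near 5% in every scenario run, and does not depend on guessing the correlation pattern.

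**What to change.** In 3.3.3, for the log-bleeding model:

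1. State that the between-brush difference in 3-month change is estimated from a group-by-visit contrast.
2. Replace the random intercept alone with an unstructured covariance across T1, T2 and T3 (six parameters), fitted by REML with Kenward–Roger degrees of freedom.
3. Name the fallback if the model does not converge: ANCOVA of the T3 value on baseline.
4. State that the p-values for this contrast come from that model and not from a SUDAAN test whose variance estimator is unspecified.
5. Correct the four repeated bleeding analyses to the three scheduled examinations.

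The cost is a few sentences of analysis wording, a few degrees of freedom in a trial planned for 4 × 25 = 100 evaluable women, and possibly wider standard errors for the 3-month change. No data collection or trial conduct changes. The wording should be settled before unblinding.
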